Group based educational programs for diabetes self-management can improve blood glucose, blood pressure, body mass index (BMI) and the requirement of blood glucose lowering drugs; however, the long-term results were varying [4]. In Italy, non-insulin-treated T2DM patients known with diabetes for at least 1 year were randomised to either group or individual care in a hospital-based setting. After 4 years clinical, cognitive, and psychological outcomes were better in the group based treatment [5]. In the DESMOND trial, greater improvements in weight loss and smoking cessation were found in the intervention group at 1-year-follow-up, but at 3-year-follow-up this effect was no longer apparent [6, 7]. In general, completers of a diabetes self-management intervention study are significantly more highly educated than dropouts [8]. This indicates that interventions to improve self-management should be tailored to different categories of patients. The ‘one size fits all’ principle in diabetes education research is outdated. To estimate a priori the chance of successful self-management of a patient, the self-management screening tool (SeMaS) can be used [9]. With SeMaS possible barriers for self-management due to depression and/or anxiety can be detected. Both depression and anxiety can interfere with the effectiveness of a self-management program at that moment for a particular person and should be dealt with before following the program. Besides, individuals with already high self-management capabilities are likely to have no additional benefit from an educational course [10–12].

We hypothesise that by differentiating between patients who may and those who may not benefit from a self-management program, a more (cost-) effective self-management education program can be designed which is also effective on the long-run. Therefore, the aim of the current study is to investigate the cost-effectiveness and long-term effects of the educational program BGI on cardiovascular risk, quality of life and diabetes self-management behaviour in a preselected group of known T2DM patients.

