### Recruitment

The electronic medical records from the people with T2DM from the participating general practitioners are scrutinised to find eligible T2DM patients. All patients who meet the inclusion criteria will be informed about the possibility to follow a group-based diabetes self-management education program with pre-selection (see further), emphasising that they will be only offered an educational program they are likely to benefit from. People can indicate on a response card whether or not they want to receive oral information about the study. If yes, a research team member will give the patient a telephone call to discuss the study. If the patient is informed and understands the information, informed consent will be completed. Once the patient has given informed consent the pre-selection will take place.

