### Pre-selection

The pre-selection procedure to assess a patient’s capabilities of self-management will be performed with the use of the SeMaS, a self-management screening tool which is validated in T2DM patients and sent to the patients home [9]. The SeMaS is a 27 item questionnaire covering self-management abilities of five psychosocial domains [locus-of-control (3 items), self-efficacy (2 items), social support (1 items), coping (9 items), anxiety (4 items) and depression (3 items)], three skills items (computer, group and self-care) and two other items including perceived burden of disease [9]. All separate items range from 0 to 3 on a 4-point Likert scale (locus-of-control, self-efficacy, coping, skills items) or from 0 to 2 on a 3-point Likert scale (social support, anxiety, depression). For all items higher scores represent higher capability, except for those in the anxiety and depression domain where higher score represent more barriers. The perceived burden of disease is scored on a visual analogue scale from 0 to 10. Patients with high scores on the domains anxiety (score >4 from total 8) and/or depression (score >3 of total 6) will be excluded during the pre-selection. Those patients first need to deal with their mood disturbance before they are able to improve their self-management skills. Patients without barriers for self-management, so with maximal self-management capacity (highest possible scores for the locus-of-control, self-efficacy, social support, coping and for anxiety ≤4 and for depression ≤3) were also excluded, since they would not benefit from the educational course. The general practitioner (GP) will be informed about the SeMaS scores of all participants.

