### Randomisation

Patients who are eligible after the pre-selection will be randomised (1:1) based on computer-generated random numbers, with sealed, opaque, sequentially numbered allocation envelopes. All patients entering the trial receive a random number from the coordinating research centre (Julius Center). Each number corresponds to either ‘BGI course’ (BGI-group) or ‘no BGI course’ (control-group). As patients will attend a course in the intervention group, it is not possible to blind participants for the treatment allocation. Patients from the same practices and general practitioners will attend a different course, so no large cluster-effect is expected.

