#### Cost-effectiveness

Data on health care resources use during the whole study period will be extracted from electronic medical records from the general practitioners and for health status the EQ 5D questionnaire will be used at baseline and after 2.5 years follow-up.

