### Cost-effectiveness

Lifetime costs and health effects (based on the EQ 5D) will be estimated using a modified probabilistic diabetes model. This validated model has been used before and is described in more detail elsewhere [28–30]. In brief, the model simulates the natural history of type 2 diabetes and calculates costs and quality-adjusted life years (QALYs) for Dutch T2DM patients [30]. The model includes a health state for cardiovascular disease (CVD; myocardial infarction, stroke, peripheral arterial disease), microvascular complications (end-stage renal disease, retinopathy and neuropathy), uncomplicated type 2 diabetes and death. The model computes the occurrence of the above-mentioned diabetes-related complications and the excess mortality due to diabetes. Based on the estimated events and prevalence of complications, it computes diabetes-related lifetime medical costs and QALYs.

To calculate lifetime costs and outcomes, each health state is assigned a value in terms of medical costs and utility (health-related quality of life), and this value is multiplied by the prevalence of the health states over time.

In addition to the model input data described above, medication costs of glucose-lowering drugs, anti-hypertensive medication and cholesterol-lowering drugs used during the total follow-up period will be included in the cost calculation. Costs of the BGI-course and total health care resources (including consultations of the dietician) use during the whole study period will also be included in the cost calculation. These costs will be extrapolated to estimate lifetime medication costs, assuming that the cost difference between the BGI-group and the control-group remains constant over time.

The model will calculate two lifetime health outcomes (life years, QALYs) and costs for each patients (discounted and undiscounted). To correct for confounding and improve model estimates of the difference in outcome between the BGI-group and the control-group, the following baseline covariates will be used: age, sex, duration of diabetes, history of cardiovascular disease, smoking, HbA1c, systolic blood pressure, total cholesterol and HDL cholesterol.

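### The ICER is sound for BGI in already screened patients, but used to judge implementation it leaves out the cost of the SeMaS screening that finds them

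*Protocol article*

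**What the plan says.** **Order of events.** Recruitment: "Once the patient has given informed consent the pre-selection will take place". Pre-selection describes SeMaS as "a self-management screening tool which is validated in T2DM patients and sent to the patients home" and adds: "The general practitioner (GP) will be informed about the SeMaS scores of all participants". Patients with high anxiety or depression scores, or with maximal self-management capacity, are then excluded. Randomisation: "Patients who are eligible after the pre-selection will be randomised (1:1".

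**Costs counted.** The Cost-effectiveness analysis section adds to the model inputs "medication costs of glucose-lowering drugs, anti-hypertensive medication and cholesterol-lowering drugs used during the total follow-up period will be included in the cost calculation", and then: "Costs of the BGI-course and total health care resources (including consultations of the dietician) use during the whole study period will also be included". The Cost-effectiveness paragraph under Measurements gives the source of the resource data: "Data on health care resources use during the whole study period will be extracted from electronic medical records from the general practitioners". The Intervention section describes the course as one individual session, four group sessions and a booster. Screening is not part of that description.

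**Comparison and use.** The ICER is BGI against control, and the Background states the aim as cost-effectiveness in a preselected group. The acceptability curve, with EUR 20,000 per QALY as an example threshold, is meant to show whether implementing BGI is cost-effective. The Background hypothesis reads, in part: "by differentiating between patients who may and those who may not benefit from a self-management program, a more (cost-) effective self-management education program can be" (the sentence ends with the design of such a programme and its long-run effect). The Abstract conclusion repeats the idea, and the Discussion counts the impact of pre-selection among the things the study will add knowledge about.

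**The concern.** The article poses two questions and defines an analysis for one of them. The defined ICER asks what BGI adds in patients who have already passed SeMaS. The statements on implementation and on pre-selection concern a different strategy: screen patients with type 2 diabetes, then train those selected. A care group adopting that strategy has to pay for screening, both of those who enter the course and of those screened out. If a care group that does not offer BGI would not screen, the whole of that cost belongs to the BGI strategy.

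Read against that decision, the effects come from a selected group while the cost of selecting them is left out. The omission is modest, but it runs in one direction and lowers the apparent cost of BGI.

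**Working it through.** **No plan figure to reproduce.** The article gives no SeMaS unit cost, number screened, fraction eligible, course cost, incremental cost or QALY gain. The only relevant number in it is the example threshold of EUR 20,000 per QALY. All other inputs below are assumptions.

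**Step 1: the defined comparison.** Let *c* be the cost of SeMaS per person screened, and C(BGI) and C(control) the other costs per randomised patient. Every randomised patient has been screened, so

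incremental cost = [C(BGI) + c] − [C(control) + c] = C(BGI) − C(control).

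The screening cost drops out and the shift is 0.

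**Step 2: screen-then-train against usual care without screening.** Let *e* be the fraction eligible after SeMaS. Finding one participant takes 1/e persons screened, so

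incremental cost = C(BGI) − C(control) + c/e.

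The added term splits as c/e = c + c(1 − e)/e. The first part is the participant's own screening, which cancels in the trial. The second is the screening of excluded patients, who belong to neither arm. With c = EUR 50 and e = 0.5 the two parts are EUR 50 and EUR 50. With c = EUR 10 and e = 0.9 they are EUR 10 and EUR 1.1.

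**Step 3: size under assumed values.** The QALY equivalent is (c/e)/20,000. The ICER shift is (c/e) divided by an assumed QALY gain per participant.

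| c (EUR) | e | c/e (EUR) | QALY equivalent | ICER shift, gain 0.05 | ICER shift, gain 0.01 |
|---|---|---|---|---|---|
| 10 | 0.9 | 11.1 | 0.0006 | 222 | 1,111 |
| 10 | 0.5 | 20 | 0.0010 | 400 | 2,000 |
| 50 | 0.9 | 55.6 | 0.0028 | 1,111 | 5,556 |
| 50 | 0.5 | 100 | 0.0050 | 2,000 | 10,000 |

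Shifts are in EUR per QALY. A wider range, c = EUR 5-50 and e = 0.9-0.3, gives 5/0.9 = EUR 5.6 to 50/0.3 = EUR 167 per participant. The ICER shift is then EUR 111-3,333 per QALY at a gain of 0.05 and EUR 556-16,667 at 0.01. Only a very small QALY gain, combined with a high unit cost or few eligible, makes the shift large against the example threshold.

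**Step 4: what belongs in c.** Sending, scoring and reporting SeMaS to the GP. The telephone call in the Recruitment section comes before consent and serves to discuss the study. It is a cost of running the trial and is left out of c.

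**The case against.** The strongest objection is that the ICER answers the question it was defined for. The comparison is BGI against control in preselected patients, and the Control group section says that the course is the only difference between the groups. A cost common to both arms should cancel. This stands in full. A reader might infer that the defined ICER is biased towards BGI, and the documents do not support that.

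A reader might also infer that SeMaS has been left out of the costing altogether. The article supports only that SeMaS is not named in any cost item. The course costs are not itemised, and a condensed article may leave the costing list to the full protocol. However, even if SeMaS were counted within the course costs, nothing in the article says so or says how the screening of excluded patients would be charged.

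A third tempting inference is that a screening cost line would let the trial test whether pre-selection improves cost-effectiveness. It would not: every randomised patient has been pre-selected, so there is nothing to compare with.

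Finally, charging screening to BGI alone assumes that a care group without BGI would not screen, which the documents do not state. Reporting SeMaS scores to the GP may also bring benefits or later costs for screened-out patients, and neither would be counted. The fraction eligible comes from people who consented to a trial and may differ in practice. These are good reasons to use a scenario and leave the base case as it is. They do not remove the mismatch between the defined ICER and the implementation question.

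**Conclusion.** The point holds as a mismatch between the ICER that is defined and the decision it is used for. For BGI against control in patients already screened, the analysis is right and the shift is zero. For the screen-then-train strategy against usual care without screening, the incremental cost is too low by c/e per participant. That is about EUR 11-100, or 0.0006-0.005 QALY at EUR 20,000 per QALY, if one assumes EUR 10-50 per person screened and 50-90% eligible. It is a one-off, modest amount in favour of BGI. The direction rests on two further assumptions: that usual care would not include SeMaS, and that SeMaS is not already within the unitemised course costs. The size rests wholly on assumed inputs.

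**What to change.** In the Cost-effectiveness analysis section:

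- State that the base-case ICER concerns BGI in patients already selected with SeMaS.
- Add a pre-stated scenario ICER and acceptability curve for the screen-then-train strategy. In it the BGI strategy alone carries a one-off cost per participant: the unit cost of sending, scoring and reporting SeMaS, divided by the fraction eligible observed in the trial. Leave out the recruitment call.
- State whether the course costs already include SeMaS, so that it is not counted twice.
- Keep this cost outside the lifetime extrapolation, which assumes a constant cost difference between the groups. A one-off cost carried through it would be counted repeatedly.
- Base conclusions about implementation on the scenario, and do not claim that the trial shows pre-selection itself improves cost-effectiveness.

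The cost is one extra line in the calculation, using the trial's own screening counts and one unit cost. Trial conduct does not change. The scenario ICER will be slightly less favourable to BGI than the base case.

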### Study design and selection criteria

The study is designed as a parallel randomised controlled trial with 2.5 years follow-up and will follow the CONSORT criteria for experimental designs [15]. Along with the BGI self-management education program (obviously only for the intervention group) all participants will receive diabetes care according to the guidelines of the Dutch College of General practitioners [16].

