### Intervention: beyond good intentions (BGI)

This study elaborates on the existing self-management program BGI [2, 17, 18]. It lasts 12 weeks and consists of one initiating 30-min individual session and four 2.5-h group sessions. In addition, one booster-session is given a few months after the last group session. The course structure is as follows:

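### The costing rule does not say consistently which costs are carried forward for life, or how trial-period resource use is kept apart from modelled lifetime costs, so incremental cost may be miscounted

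*Protocol article*

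**What the plan says.** The rule is in the protocol article, in the Cost-effectiveness section that follows Statistical analyses. It builds cost in layers.

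- **Model.** A diabetes model simulates events and complications, and from these "it computes diabetes-related lifetime medical costs and QALYs". To do so, "each health state is assigned a value in terms of medical costs and utility (health-related quality of life"), and that value is multiplied by the prevalence of the state over time. Uncomplicated type 2 diabetes is one of the listed states.
- **First addition.** The text continues: "In addition to the model input data described above, medication costs of glucose-lowering drugs, anti-hypertensive medication and cholesterol-lowering drugs", as used during follow-up, enter the calculation.
- **Second addition.** "Costs of the BGI-course and total health care resources (including consultations of the dietician) use during the whole study period will also be included".
- **Extrapolation.** The next sentence reads "These costs will be extrapolated to estimate lifetime medication costs, assuming that the cost difference between the BGI-group and the control-group remains constant".

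The Intervention section describes the course as time-limited: "It lasts 12 weeks and consists of one initiating 30-min individual session and four 2.5-h group sessions", plus one booster a few months later. The observation period is fixed under Study design and selection criteria: "The study is designed as a parallel randomised controlled trial with 2.5 years follow-up". Incremental cost is the numerator of the ICER, which the article names as the primary outcome of the cost-effectiveness analysis and sets against a willingness-to-pay threshold, with 20,000 euro per QALY as the example.

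**The concern.** Three features of the rule leave the ICER numerator open.

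1. **What is extrapolated.** The nearest costs to which the extrapolation sentence can refer are the course and total resource use, but the sentence says that the result is lifetime medication cost. Neither the course nor general resource use is medication, so both halves of the sentence cannot be right. If an analyst follows the first half, a course delivered once becomes a recurring cost in the BGI arm only.
2. **Overlap.** The model prices health states over a lifetime that includes the trial period. Observed total resource use for that same period is then added. Neither a split in time nor a removal of cost categories is stated.
3. **Constant difference for life.** On either reading of the first feature, a cost difference observed over 2.5 years is held fixed for life, and no other scenario is stated. The article's own Background reports a comparable programme with an effect on weight and smoking at 1 year, for which "at 3-year-follow-up this effect was no longer apparent".

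Two analysts working from this text could produce different incremental costs, and so different ICERs, from the same data.

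**Working it through.** The plan gives no course price, unit cost, cost difference, horizon in years or discount rate, so there is no figure of its own to reproduce. What follows is illustrative. Horizons and discount rates are assumptions.

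**Step 1. Course cost under the two readings.** Let C be the one-off course cost per patient. Seen over 2.5 years, it is C/2.5 per year. If that difference is held constant over a horizon of L years at discount rate r, the amount charged is

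C × A(L, r) / 2.5, with A = L if r = 0, and A = (1 − exp(−rL)) / r otherwise.

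| Assumed horizon | r = 0 | r = 4% |
|---|---|---|
| 10 years | 10/2.5 = 4.0 × C | 8.24/2.5 = 3.3 × C |
| 20 years | 20/2.5 = 8.0 × C | 13.77/2.5 = 5.5 × C |
| 30 years | 30/2.5 = 12.0 × C | 17.47/2.5 = 7.0 × C |

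On the medication-only reading the charge is 1.0 × C in every row. The control arm has no course, so under the literal reading nothing cancels and the error is always upward.

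**Step 2. Overlap of observed and modelled costs.** Let dR be the BGI-minus-control difference in trial-period resource use, and s the share of that use already contained in the health-state costs. The error in incremental cost is s × dR.

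- s = 0 or dR = 0: no error. Equal overlap in both arms cancels.
- Assumed dR = +300 per patient (any currency unit), s = 0.5 to 1: incremental cost is overstated by 150 to 300.
- Assumed dR = −300, s = 0.5 to 1: incremental cost is understated by 150 to 300.

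The quantity that matters is therefore the between-arm difference in overlapping use, not the total 2.5-year cost in each arm. The article fixes neither s nor the sign of dR.

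**Step 3. Weight of the constant-difference assumption.** This applies on either reading. With a constant yearly difference and no discounting, the share of the lifetime medication cost difference that lies beyond the observed period is (L − 2.5)/L: 7.5/10 = 75%, 17.5/20 = 87.5% and 27.5/30 = 92% at the three assumed horizons. Most of that component is assumed rather than observed.

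**The case against.** The strongest reply is that the extrapolation sentence names its own target. It speaks of lifetime medication costs, the paragraph opens with medication costs, and nothing suggests that the course is repeated. On that reading the course is counted once and the fault is one of wording. This stands: the multiples in the table describe what the literal text permits, not what the analysis is known to do.

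On overlap, the contents of the health-state costs are left to cited model descriptions that are not at hand, and the model is described as modified. Trial resource use comes from general practice records, which may cover different items. This also stands. Overlap is possible, because uncomplicated diabetes is a priced state and the added resource use is described as total, but it is not shown.

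A reader might infer that incremental cost is overcounted, or that the cost-effectiveness conclusion could be reversed. The text supports neither. Only the course-cost part has a definite direction, and only on the literal reading. The overlap part can go either way. Without a course price or a QALY gain, no effect on the conclusion can be calculated.

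On the constant difference, the assumption is stated openly, and an article may leave scenario lists to a fuller plan. The faded effect in the Background concerned weight and smoking, not medication cost, and the same section cites a group programme with better outcomes at 4 years. So the Background does not show the assumption to be wrong. It does show that persistence is uncertain, which is reason enough to report an alternative beside it.

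What the reply does not remove is that the article states a specific costing rule whose two halves disagree. This is a rule badly fixed, not detail left out.

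**Conclusion.** The point holds as an inconsistent and incomplete costing rule, not as a demonstrated bias. Under the literal reading the one-off course cost would enter incremental cost about 3 to 12 times, given assumed horizons of 10 to 30 years, discounting of 0 to 4% and annualisation over 2.5 years. Under the medication-only reading it enters once. Nothing in the stated rule prevents overlap between trial-period resource use and modelled costs. Its effect on incremental cost equals the overlapping share times the between-arm difference in use, so its size and sign are open. The constant lifetime difference is the only scenario stated and carries most of the lifetime medication cost difference on any reading.

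Cost-effectiveness is a secondary outcome of the trial, but it is part of the stated aim, and the ICER depends directly on this rule. The change should be made before the cost data are analysed.

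**What to change.** Amend the Cost-effectiveness section as follows.

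1. State that only recurrent medication costs are extrapolated beyond the trial.
2. Book the BGI course and the booster session once, at the time of delivery.
3. Use observed costs for 0 to 2.5 years and modelled costs afterwards. Alternatively, remove from the observed costs the categories that the health-state costs already include, and list them.
4. Next to the constant-difference result, report a scenario in which neither costs nor risk factors differ between the groups after 2.5 years.

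The cost is rewording and a few extra model runs. No new data are needed.
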